#### Guided Rest + Enhanced Graded Exertion (EGE Arm)

Participants in the EGE arm complete the activities described above and guided rest prior to progressing past Stage 1 of the graded exertion (Table 1) (16). The term EGE was chosen as sites are directed to be sports specific in their choice of activities throughout the progression. A medical professional determines the symptom status of the athlete and when Stage 2 of the graded exertion for return to sport will begin. Once the athlete has been asymptomatic for 24 h (within at least 85% of their baseline symptom score—definition of asymptomatic for the study) they may begin the EGE progression. This protocol follows the 5th International Consensus Statement on Concussion in Sport return to sport strategy (16), but encourages enhancement to include sports and skill specific activities. Each step is recommended for completion on a separate day, at the clinician's discretion. Clinicians complete session logs for each graded exertion session for Stage 2 and for subsequent stages that include the following information: initial symptom checklist, phase of graded return to play progression, specifics on session activities, percentage of rest during the session, participants rating of perceived exertion, final symptom checklist, session satisfaction rating, and overall session feedback.

#### Guided Rest + Multidimensional Rehabilitation + Enhanced Graded Exertion (MDR Arm)

The term MDR was chosen to illustrate more than one area of activity would/could be addressed. Participants in the MDR arm complete the same activities as the EGE arm participants (as described above). However, once the participants' symptoms become “stable” (i.e., not getting worse), they are progressed into the MDR activity phases. “Stable” is defined as no significant increase utilizing Reliable Change Indices (RCI) metrics [symptom score not increasing by 10 or more over a 24-h period from their initial (first) symptom assessment] and no significant development of new symptoms over 24 h. Prior to beginning the exercises in the intervention, clearance to do so is obtained and documented by the athlete's healthcare team. The intervention includes 5 progressive phases: symptom control, perceived impairment reduction, activity integration, recovery acceleration, and sport specific application (Figure 2).

**Figure 2 F2:**
[figure not shown]
Multidimensional Rehabilitation (MDR) framework and progression.

The choice of activity type in each phase is dependent on the nature of the athlete's reported symptoms and noted assessment deficits via a symptom assessment and clinical interview at each phase. Once an athlete is asymptomatic these activities may be chosen based on sport-specific performance needs. Activities are grouped into categories (termed “buckets”) that are matched to a participant's symptom reports (Figure 3). The activity “buckets” include: balance, cognitive, comfort (symptom/emotional stability), and visual-vestibular. Some symptoms do not necessarily match the activity buckets and should be monitored. Activities that meet the intensity of targeted buckets are selected by the clinician, and are extensively documented, similar to the documentation process utilized by Schneider et al. (12).

**Figure 3 F3:**
[figure not shown]
Symptom presentation and activity bucket matches for the Multidimensional Rehabilitation (MDR) progression.

Active, MDR sessions consist of guided exercises directed by a team clinician. Participants are asked to complete four sessions per week until full return to play, at their healthcare team's discretion. During each session, clinicians complete session documentation logs that include the following information: initial symptom checklist, phase of graded return to play progression, specifics on session activities, percentage of session spent resting, participants rating of perceived exertion, and final symptom checklist, session satisfaction rating, and session feedback. Should a participant state they are feeling worse during a session or request to stop, symptoms will be immediately assessed by the clinician. Sessions are stopped if a participant exceeds reliable change on total symptom severity (10 or more total point increase) (18, 19), if the participant requests to stop, or if the provider feels the participant is too symptomatic to continue. The symptom scale utilized is the SCAT 22-item (each item scored 0–6) post-concussion symptom scale. The metric utilized from this is total symptom burden (severity), which is calculated by summing the score of each item for a possible score range of 0–132.

Progression through the MDR protocol follows a standardized set of rules (Table 2). Progression from Phase I (Symptom Control) to Phase II (Perceived Impairment Reduction) requires that an individual's symptoms must not increase 10 or more points compared to their lowest symptom assessment since injury, and they must not have any symptoms with a symptom score of 5 or 6 at the beginning of a subsequent intervention session. When the participant completes activities in the phase where symptoms remain stable/do not increase beyond reliable change from beginning of one session to beginning of another (see “stable” above), the participant will be progressed to the next phase. We expect some increase from beginning to the end of a session, but we expect this to decrease by the start of the next session. Participants should on average, complete four sessions per week until fully returned to play. One session each week may be completed at home (i.e., unsupervised) as directed by a team healthcare provider. Each session lasts ~20 min and is conducted at the clinician's discretion. Once enrolled into the MDR study arm, each participant completes a minimum of two sessions in Phase I (Symptom Control). The MDR activities may commence prior to beginning the EGE progression and should be integrated with EGE activities once a participant is asymptomatic.

**Table 2 T2:** Multidimensional rehabilitation progression (Active Rehab).

**Rehabilitation stage**	**Notes**	**Goal**
**Entry into Phase I** (to the intervention progression)	*Symptoms not getting worse*. ∘ Symptom score not increasing by 10 or more over a 24 h/1 day period from their initial symptom assessment (6 h or 24–48 h assessment) ▪ Most people will be eligible at this time ▪ The earliest someone could start the intervention would be 24–48 h post-injury	Stabilization of symptoms
**Phase I**	*Must complete a minimum of **2 sessions** in this phase* Progression to Phase I may occur when: ∘ An individual's symptoms must **not** increase 10 or more points **compared to their lowest symptom score since the injury** ∘ They must not have any individual symptom items with a severity score of **5 or 6** when assessed at the beginning of a subsequent intervention session at Phase II (this would be the third session or beyond)	Symptom control and introduction to the intervention
**Phases II–III, Phases III–IV, and Phases IV–V**	*Must be a minimum of 1 day spent at each phase. Two phases cannot be completed on the same day*. Progression from one of these phases to the next (2–3, 3–4, and 4–5) may occur when: ∘ An individual's total symptom severity score does **not** increase by 10 or more points from beginning of one intervention session to beginning of the subsequent session ∘ No individual symptom item severity score symptom score at the beginning of the subsequent intervention session is a **5 or 6**	Phase II- Perceived Impairment reduction Phase III- Activity integration Phase IV- Recovery acceleration Phase V- Sport specific application
**Considerations for care and progression** Clinicians should consult their site medical team regarding issues of pre-existing conditions and presentation that may affect care. Some of these may include:		
Migraine headaches Sleep related conditions/symptoms Gross vestibular dysfunction		
Documentation of all additional care and treatment should be completed including but not limited to:		
Medications Additional therapies (e.g., physical therapy, vision therapy, vestibular therapy, etc.) All referral sources and those involved in the individual's care		
**Return to full participation**		
Return to full participation will occur at the physician/site medical professional's discretion of patient full recovery and will be documented. The intervention progression will stop.		

Specifically, progression from one phase to the next in Phases II through V requires that the participant does not experience any significant increase in symptoms from the beginning of one intervention session to the beginning of the subsequent session (as measured by a RCI of 10 of more total severity point increase), and no symptom score at the beginning of an intervention session is a 5 or 6 on the self-reported symptom severity scale. Once determined to be clinically recovered (“asymptomatic” by study definition or at clinician discretion), they begin the EGE progression (16) (Table 1) with sport and skill specific enhancements at each phase. This MDR protocol should not delay the return to play process as when the participant becomes “asymptomatic” (by the study definition) they begin the enhanced graded return protocol (as the standard of care states) and will continue MDR exercises throughout this process. MDR activities are integrated with the return to sport progression at each Stage once the return to sport progression begins (Figure 4). Participants continue the rehabilitation progression during the EGE protocol and may continue the MDR exercises after full return for maintenance and/or to complete the last phases of the MDR progression at their clinician's discretion. Figure 5 provides an example of cognitive activity progressions through each Phase. The Supplemental Table 1 outline activity “bucket” progressions by MDR phase.

**Figure 4 F4:**
[figure not shown]
Example illustration of Multidimensional Rehabilitation (MDR) activities being integrated to the Enhanced Graded Exertion (EGE) progression. This figure illustrates the overlap in activities. MDR activity may be integrated as soon as the participant is asymptomatic.

**Figure 5 F5:**
[figure not shown]
Example Balance Activity Progression through the Multidimensional Rehabilitation (MDR) framework. Written informed consent was provided by all individuals in the images for publication.

### Safety Procedures

As with any trial, safety-related procedures were decided *a priori* by the study team in concordance with current literature. Potential risk of the study assessments and interventions were evaluated. Based on previous studies and clinical fortitude, it was determined *a priori* that discomfort is likely (10–25%) to occur as the participants are progressed in the interventions. We specifically anticipated more discomfort among those in the multidimensional activity group, as discomfort may increase slightly during rehabilitation sessions, as often occurs within any type of rehabilitation session. All rehabilitation is monitored and progressed by medical professionals and individuals are referred to their team physician as deemed medically appropriate. If at any point the participant or clinician feels the intervention should be discontinued, this is done and documented. Injury risk is rare, however, there is the small possibility that symptom exacerbation or injury may occur during the interventions or testing. As all participants will be studied and progressed in environments with medical professionals, any potential significant symptom exacerbation or injury is documented, and participants are referred to the physician at the institution as deemed appropriate. The physician and medical team at each site will determine status and ability to continue the study activities. All events of this nature are documented appropriately via study administrative forms. A symptom-based adverse event was determined to be, as outlined in the progression, if an individual's symptoms increased by a reliable change of 10 or more points and remained elevated at that change in the subsequent session. An independent safety officer reviews quarterly study safety reports provided by the study team study and provides feedback on any overall concerns or safety issues. If the safety officer deems the study unsafe after corrective actions have been put into place, the study will be halted, or significant changes may be made to the study methods.

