**Figure 7 F7:**
[figure not shown]
Dual-task schematic. **(A)** Memory task begins, **(B)** walking task, and **(C)** memory recall.

**Daily Activity and Symptom Tracking**: All concussed participants complete a daily activity and symptom tracking survey (cognitive and physical) from time of injury through 7 days post return to play. The survey can be completed on paper or via Qualtrics and includes questions about mental and physical activity as well as symptoms. *Time point collected: Daily through 7-days post return to play*.

**Participant Satisfaction**: The participant will be asked to complete a questionnaire regarding his/her satisfaction with the rehabilitation sessions and the intervention. This measure is adapted from the PSQ-18 which is a publicly available scale that measures general athlete satisfaction with care. The PSQ-18 was designed based on feedback from athletes using input from providers about the care they receive and has been used in various settings. *Time point collected: 7 days post return to play*.

**Concussion Injury Index**: This form documents all aspects of a participant's concussion. It is completed by the clinical research staff at the study site. Information gathered on this form includes: sport at time of injury, number of years playing sport, date and time of injury, date reported injury, loss of consciousness, etc. *Time point collected: This form is to be completed over the course of the injury and should be finalized by the 1-month post-return to play time point*.

**Recovery Tracking**: A recovery tracking form documents all aspects of a participant's recovery from a concussion. It is completed by the clinical research staff at the site throughout the time it takes the participant to recover. Length of symptoms, medication usage, therapies/treatments, psychiatric issues, and return to play information will be reported. It also includes information on completion or discontinuation of the study treatment activities (e.g., discontinuation of the intervention for medical reasons). *Time point collected*: *This form should be completed over the course of the injury and should be finalized by the time entry is completed for the 1-month post-injury assessment*.

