## Ethics and Dissemination

The study is carried out in accordance with international standards of research and under the guidance of the data coordinating center Institutional Review Board. Additional approvals and reviews are conducted as necessary for all study sites. Consideration is given to local needs and cultural considerations in the ethics review and implementation process. Written, informed consent is provided by each participant. For minors in the high school cohorts, guardian consent is also obtained. The trial is registered at clinicaltrials.gov (NCT02988596). Participants are enrolled at pre-season baseline to provide an opportunity to consent prior to a concussion occurring and reduce respondent burden post-injury. The model consent form may be obtained from the corresponding author upon request. All intervention and study activities occur with site medical professional guidance. Site investigators and clinicians explain the study protocol to participants are available to participants for questions and concerns. After completion of the trial and statistical analysis of the trial data, findings will be published in peer-reviewed medical journals and will adhere to CONSORT standards. The current plans for these primary papers include: (1) a primary paper addressing effectiveness of the intervention arms on the primary outcomes of time to clearance for full return to sport and time to asymptomatic, (2) a paper addressing effectiveness of the interventions on the secondary clinical outcomes, (3) a paper concerning overall safety and symptom provocation for both intervention arms, and (4) a paper addressing implementation evaluation and feasibility of the study interventions. Additional dissemination of results will include presentation at relevant scientific meetings, to the general public, and through peer-reviewed publications.

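### The symptom-based adverse event needs a persisting rise at the next session, but EGE logs no sessions before the athlete is asymptomatic, so its prevalence by arm is not comparable

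*Protocol article*

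**What the plan says.** The Safety Procedures section ties the symptom-based adverse event to the progression: it occurs when "symptoms increased by a reliable change of 10 or more points and remained elevated at that change in the subsequent session".

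The EGE Arm section starts the exertion progression "Once the athlete has been asymptomatic for 24 h". Its documentation starts at the same point: "Clinicians complete session logs for each graded exertion session for Stage 2 and for subsequent stages". On pace, it says "Each step is recommended for completion on a separate day", subject to the clinician's discretion.

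The MDR Arm section says "The MDR activities may commence prior to beginning the EGE progression". Table 2 adds "The earliest someone could start the intervention would be 24–48 h post-injury". MDR athletes are asked for four sessions per week, with at least two in Phase I. Under Symptomology, checklists are taken at the start and end of each intervention session.

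Under Daily Activity and Symptom Tracking, "All concussed participants complete a daily activity and symptom tracking survey", from injury to 7 days after return to play. The adverse event definition does not refer to this record.

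For Specific Aim 2, the Planned Data Analysis gives descriptive statistics that include adverse event prevalence. Ethics and Dissemination plans "a paper concerning overall safety and symptom provocation for both intervention arms".

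**The concern.** The event can be observed only where there are sessions, and the arms differ by design in when sessions begin. The symptomatic phase is where a sustained rise in score would be of most interest. In that phase MDR athletes are assessed at sessions and EGE athletes are not. If prevalence is set out by arm, MDR gains events from extra opportunities to observe them, and worsening during EGE guided rest does not receive this label. A reader of the safety paper could not separate symptoms provoked by early activity from symptoms that were merely recorded more often. The article openly expects more discomfort in MDR, which makes that separation important.

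**Working it through.** The plan gives no figure for this event, so there is nothing to reproduce. The structural result comes first, then an illustration of size.

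**Opportunities before the athlete is asymptomatic**

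- EGE: no logged session, so no pair of successive sessions and no way to meet the definition. This needs no assumption beyond athletes following the protocol.
- MDR: at least 2 sessions (the Phase I minimum), otherwise about 4/7 per day from the start of sessions.

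**Inputs**

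- Four sessions per week; earliest start 24–48 h after injury, taken here as day 2 (MDR Arm section, Table 2).
- Days to asymptomatic, D: not stated. The Table 4 column labels (4/7, 4.5/7 and so on) suggest 7 days for EGE and shorter values for MDR. Values of 4.5, 7, 10 and 14 are assumed.
- Risk p that a session pair meets the criterion: not stated. 2% and 5% are assumed, equal in both arms.

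**Formulas**

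- MDR sessions before asymptomatic: n = 4/7 × (D − 2), rounded, with a minimum of 2.
- Session pairs: n − 1.
- Probability of at least one event: 1 − (1 − p)^(n − 1).

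For D = 7: 4/7 × 5 = 2.86, so about 3 sessions and 2 pairs. Then 1 − 0.98² = 4.0% and 1 − 0.95² = 9.8%.

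| D (days) | MDR sessions | Pairs | MDR, p = 2% | MDR, p = 5% | EGE |
|---|---|---|---|---|---|
| 4.5 | 2 (minimum; formula gives 1.43) | 1 | 2.0% | 5.0% | 0% |
| 7 | 3 (2.86) | 2 | 4.0% | 9.8% | 0% |
| 10 | 5 (4.57) | 4 | 7.8% | 18.5% | 0% |
| 14 | 7 (6.86) | 6 | 11.4% | 26.5% | 0% |

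**Whole course**

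The EGE zero covers one phase only. With one session at each of Stages 2–5, EGE has 4 sessions and 3 pairs. If MDR has the same 4 sessions after becoming asymptomatic (assumption), D = 7 gives 3 + 4 = 7 sessions and 6 pairs.

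- p = 2%: EGE 1 − 0.98³ = 5.9%; MDR 1 − 0.98⁶ = 11.4%; ratio 1.9.
- p = 5%: EGE 1 − 0.95³ = 14.3%; MDR 1 − 0.95⁶ = 26.5%; ratio 1.9.

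Without rounding, MDR has 3 + max(2, 4/7 × (D − 2)) pairs. Over D from 4.5 to 14 days and p from 2% to 10%, the apparent risk ratio runs from about 1.5 to 3.1, although the risk per pair is identical in both arms.

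**The case against.** The strongest reply is that the definition serves a legitimate purpose. It counts symptoms provoked by supervised activity, which is the safety worry set out in the Introduction, and over-counting in the new arm is the cautious direction for monitoring. That stands as a reason to keep the session-based event, but not as a reason to set its raw prevalence side by side.

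A second reply is that Aim 2 is descriptive and no formal test between arms is stated. This also stands and limits the point. Unequal observation still distorts a descriptive table, and both prevalence and a paper covering both arms are planned.

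Some stronger readings are tempting, but the documents do not support them:

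- A reader might infer that worsening under EGE goes unseen. It does not: both arms complete the daily survey, significant exacerbations are documented, and symptom trajectories are a secondary outcome. What is missing is this one label.
- A reader might infer that the quarterly safety-officer reports, or Aim 2 as a whole, rest on these counts. The article does not give the content of those reports and lists other inputs to Aim 2.
- A reader might infer that the trial cannot show both arms to be safe. The article states an expectation of safety, and other safety data are collected.
- A reader might count four looks in the first week, giving 8–19% at the same assumed risks. The delayed start and the need for two successive sessions bring this down to about 2 pairs.

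Finally, the article does not say that the daily survey carries the 22-item, 0–132 score, and the Symptomology collection points do not name it. This reservation stands, so the fix needs a fallback.

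**Conclusion.** The point holds in a limited form. As written, the definition gives MDR opportunities to register an event during the symptomatic phase and gives EGE none, so the prevalence of this event should not be read as a comparison of arms. The EGE zero in that phase follows from the text. The MDR figure of about 4–10% is an illustration that depends on recovery at day 7, sessions from day 2 and an assumed 2–5% per pair; it would be 2–5% at 4.5 days and about 11–27% at 14 days. Only this descriptive symptom-based event is affected. Injuries, serious events, other documented exacerbations, time to asymptomatic and time to clearance are not. The change is worth making before any table by arm is produced.

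**What to change.** 1. For any statement by arm, derive the symptom event in both arms from the daily symptom record: a rise of 10 or more points still present at the next daily score, from the first assessment to 7 days after return to play. Name one reference score for the rise and apply it in both arms, because the Safety Procedures section names none and Table 2 uses several. Report the event per athlete and per day at risk.
2. Keep the session-based event as a measure of activity-provoked symptoms, reported per session.
3. First confirm that the daily survey carries the 22-item severity score. If it does not, compare session-based events only over the graded-exertion stages that both arms share, per session. Report MDR events before the athlete is asymptomatic separately and mark them as non-comparative.

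The cost is a change to the definition and one derivation if the daily score exists; the fallback uses session logs already kept. The main downside is incomplete self-completed diaries, possibly to different degrees by arm, so daily completion should be reported by arm.
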